##### Adverse events, serious adverse events, and complications

The following absolute differences in proportions will be estimated using the treatment coefficient obtained from a binomial regression model with the identity link function:
Proportion of patients experiencing at least one AEProportion of patients experiencing at least one SAEProportion of patients with at least one recorded complication (any complication)Proportion of patients requiring revision ankle surgeryProportion of patients experiencing reoperation other than revisionProportion of patients experiencing surgical site infection

Relative risks will be obtained from a binomial regression model with the log link. If convergence is an issue a Poisson regression model with the log link and robust error estimates will alternatively be fitted to obtain relative risks.

Unadjusted treatment differences will initially be obtained for each of the event outcomes. The models will then be extended to adjust for presence of OA in each of the two adjacent joints (OA1, OA2). Due to potential sparse data in these outcomes, the models will not adjust for surgeon.

The distribution of the AEs and SAEs per patient will also be presented descriptively, but no formal analysis will be performed.

### Additional analyses

#### Subgroup analyses

An exploratory subgroup analysis will be performed to investigate whether there is any interaction between the effect of treatment and the presence of OA in each of the two adjacent joints on the primary outcome.

The fitted primary analysis model will be extended to include the interactions between treatment and presence of OA in each of the two adjacent joints. As the trial has not been powered to detect this, the analysis will have limited power and is exploratory. We would anticipate that the outcomes in TAR patients at 52 weeks are better than arthrodesis patients when there is osteoarthritis in adjacent joints.

Further exploratory subgroup analyses will be undertaken similarly to investigate whether there is any interaction between patient preference (TAR, arthrodesis, or no preference) and the effect of the treatment to which the subjects are subsequently allocated, and whether there are any interactions between treatment and age, sex, or significant mal-alignment pre-surgery (as measured on plain AP radiographs, i.e. tibiotalar angle). The fitted primary analysis model will be extended to include the interaction between treatment and the associated variable for each test.

All subgroup analyses are hypothesis generating and will not form the basis of conclusions drawn from the trial.

#### Sensitivity analyses

The robustness of the results to assumptions made about missing data in the primary outcome will be assessed. The primary analysis is only valid if the distribution of the 52-week MOXFQ scores are not different between the responses which are observed and those which are unobserved (conditional on all baseline response and covariates, treatment, and 26-week post-op response), i.e. if these data are missing at random.

Firstly, characteristics of patients missing a 52-week response will be investigated using logistic regression, with an indicator for missing data modelled on baseline covariates and the data items collected at 26 weeks post-op. Results from the model will provide contextual information regarding the missing data and, together with qualitative information gathered from the site teams, will be used to explore potential mechanisms for missing data.

Secondly, if more than 10% of patients operated on are missing 52-week MOXFQ scores (the attrition assumed in the original sample size calculation), a sensitivity analysis will be done to explore the impact of the primary outcome data being missing not at random (MNAR). A pattern mixture modelling approach will be adopted for the analysis [25]. It will explore how different the unobserved responses would have to be from the observed responses for inferences from the primary analysis to change; specifically, how extreme the departure from MAR would have to be for the *p* value to change from *p* < 0.05 to *p* ≥ 0.05 (or *p* ≥ 0.05 to *p* < 0.05).

In brief, multiple imputation will be used to produce and analyse datasets with 52-week MOXFQ imputed on the assumption that it is missing randomly conditional on the other recorded variables. The number of imputation datasets created, n, will be chosen to give a power reduction of < 1% compared to using *n* = 100 [26]. Then, the imputed 52-week MOXFQ scores will each have a number Ø added to them, and the multiple imputation primary analysis model will be run (with estimates combined using Rubin’s rules [27]). The value of Ø which causes the *p* value for the 52-week treatment effect estimate to cross the 0.05 boundary will be identified and reported. This number is interpretable as how different MOXFQ would have to be from expected amongst the patients who did not attend at 52 weeks for the analysis conclusions to change. The possibility that data are MNAR in one treatment group only will also be explored: only imputations in the TAR group will be edited (missing data for the arthrodesis group remain imputed under MAR) and the Ø which causes the 52-week treatment effect estimate to cross the 0.05 boundary will be identified. Subsequently, only imputations for the arthrodesis group will be modified as described above. Alongside information on the characteristics of the patients missing 52-week MOXFQ scores, these analyses will be used to consider whether missing outcome data may compromise conclusions from the primary analysis.

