## Background

End stage ankle osteoarthritis (OA) causes pain and chronic disability [1, 2]. It has been estimated that at least 29,000 patients with symptomatic ankle OA are referred to specialist foot and ankle surgeons each year in the UK, and that around 3,000 will choose to undergo surgery with the NHS [3]. The main surgical treatments for end-stage ankle OA are total ankle replacement (TAR) or ankle arthrodesis (fusion) [4]. Improvements in pain-free function and quality of life have been reported for both TAR and fusion, but there has never been a prospective randomised trial directly comparing the two treatments [5].

TARVA is a parallel-group, non-blinded randomised controlled trial that will compare clinical outcomes and cost-effectiveness of TAR versus ankle arthrodesis in patients with end-stage ankle Osteoarthritis (OA). Full details of the background to the trial, the interventions under study and its design are in the published trial protocol [6]. From March 2015 to January 2019, 303 patients were randomised to surgery at one of 17 surgical centres participating in the trial in England, UK.

This article describes the statistical analysis plan for the TARVA trial. Analyses will commence in February 2020 following completion of 52 weeks follow-up for the last patient, data cleaning checks, and data lock. The analysis of the primary outcome will be independently programmed from the cleaned derived dataset by a statistician who did not perform the main analysis, and in parallel by the trial statistician.

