## Outcomes

### Primary outcome measure

The primary outcome measure is the absolute difference between the two treatment arms in self-reported pain-free function, as measured by the Manchester-Oxford Foot Questionnaire (MOXFQ) walking/standing domain score [8] at 52 weeks post-op. The 52-week score will be used if it was taken in a window from 48 to 56 weeks post-op.

The MOXFQ standing/walking domain score has been found to be a valid and responsive measure to evaluate all types of foot and ankle surgery [9, 10], and it has additionally been shown to be more responsive for the outcomes of foot and ankle surgery patients than generic QoL measures such as the EuroQol five-dimension quality-of-life instrument (EQ-5D) and the Short Form (36) Health Survey (SF-36) [11].

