## Analysis principles

### Patient population to be included in analysis

The main analysis will be conducted on an intention-to-treat (ITT) basis; all observed outcome data from patients according to their randomised surgical procedure will be used, irrespective of type of surgery received or whether surgery was performed. Sensitivity analysis (described below) will assess the impact of missing outcome data.

Additionally, if cross-over prior to surgery does occur, a per-protocol (PP) analysis will be performed for the primary outcome that only includes data from patients who undergo surgery according to their randomised surgical procedure. The FAAM-Sport questionnaire is only completed by patients who indicate they are involved in sports. Analysis of the FAAM-Sport domain will therefore always be based on the subgroup of patients who indicate they are involved in sports at baseline, following the above principles.

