### Follow-up and losses to follow up: missing data

Missing baseline covariate data are not anticipated since covariates must be recorded to allocate treatment.

We expect that up to 10% of patients will not provide measurements at 52 weeks post-op. Numbers and percentages of missing data at each visit (baseline, weeks 26 and weeks 52) will be tabulated by treatment group for the primary and secondary outcomes (Additional file 1: Table S2).

All observed data will be included in the primary and secondary analyses. Missing outcome data will be assumed to be missing-at-random (MAR) conditional on the observed values of all other variables included in the analysis models, and so independent of the values of the unobserved data itself. As the primary outcome is the change from baseline, patients without baseline and at least one outcome score will consequently not be included in the analysis. Their inclusion, however, would not add any information to the analysis [21].

The characteristics of patients missing 52-weeks MOXFQ data will be evaluated and a sensitivity analysis will be done to examine the impact of departures from the MAR assumption (described below).

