### Trial treatment

The number of patients undergoing their randomised surgery will be reported by treatment group. Although it is made explicit that patients cannot change surgical treatment arm once it has been randomly allocated, the clinician remains free to give alternative treatment to that specified in the protocol if it is felt to be in the best interest of the patient. Any cross-overs or other treatment deviations, as well as the number of patients who did not undergo surgery of any kind, will be specified along with reasons, as detailed in the protocol deviation log.

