## Abbreviations

AE: Adverse event
AP: Anteroposterior
CT: Computed tomography
EQ-5D: EuroQol five-dimension quality-of-life instrument
FAAM: The Foot and Ankle Ability Measure
FAAM-ADL: The Foot and Ankle Ability Measure Activities of Daily Living subscale
FAAM-Sport: The Foot and Ankle Ability Measure Sport subscale
ICC: Intra-class correlation coefficient
ITT: Intention-to-treat; includes all observed data from randomised patients in accordance with their randomised procedure, regardless of whether surgery actually occurred
m: Average cluster size (patients per surgeon)
MAR: Missing-at-random
MCID: Minimal clinically important difference
MI: Multiple imputation
MNAR: Missing-not-at-random
MOXFQ: The Manchester-Oxford Foot Questionnaire
MRI: Magnetic resonance imaging
OA: Osteoarthritis
PIS: Patient information sheet
QoL: Quality of life
ROM: Range of motion
SAE: Serious adverse event
TAR: Total ankle replacement
TARVA: Total Ankle Replacement Versus Arthrodesis trial
T-score: A measurement of bone density expressed in standard deviation units from that of a healthy young adult
UCL CCTU: UCL Comprehensive Clinical Trials Unit
VAS: Visual analogue scale

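### The trigger for the MNAR tipping-point analysis counts only operated patients and pools the arms, so it can stay unmet when well over 10% of randomised patients lack a 52-week score

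*SAP article*

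**What the plan says.** Under Sensitivity analyses, the SAP article starts with an unconditional logistic regression that describes who lacks a 52-week response. A pattern-mixture analysis then follows only on a condition: it is done "if more than 10% of patients operated on are missing 52-week MOXFQ scores (the attrition assumed in the original sample size calculation". When run, it multiply imputes the 52-week score under MAR and shifts the imputed values until the p value crosses 0.05. The shift is applied in both arms together, then in each arm alone.

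Four other places bear on that condition:

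- **Analysis population.** Observed outcome data are used by randomised procedure "irrespective of type of surgery received or whether surgery was performed". The Abbreviations entry for ITT agrees: it "includes all observed data from randomised patients in accordance with their randomised procedure, regardless of whether surgery actually occurred".
- **Expected loss.** The missing-data section says: "We expect that up to 10% of patients will not provide measurements at 52 weeks post-op". This is not restricted to patients who had surgery. The same section adds that "patients without baseline and at least one outcome score will consequently not be included in the analysis".
- **Timing of the primary score.** "The 52-week score will be used if it was taken in a window from 48 to 56 weeks post-op". No other time origin is given.
- **Patients without surgery.** The Trial treatment section foresees them and will report "the number of patients who did not undergo surgery of any kind", with reasons.

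**The concern.** The trigger is meant to protect an ITT analysis, yet its base is a post-randomisation subset. A patient who is randomised, never operated on and never scored is missing from the ITT comparison but adds nothing to the count that decides whether an MNAR analysis is done. The trial is unblinded and allocation is known at once, so loss between allocation and surgery could plausibly be related to outcome. That is the kind of loss an MNAR analysis exists to examine.

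The condition also uses one rate pooled over both arms. The analysis that it gates explicitly considers data being MNAR in one arm only, and the pooled rate is insensitive to that situation.

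At stake is whether the only MNAR analysis in the plan is carried out when loss among randomised patients exceeds the level that the plan itself names.

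**Working it through.** **Inputs.** From the Sample size section: difference 12, SD 27, 90% power, 5% level, 10% loss, 118 per arm before clustering, m = 14, ICC = 0.03, f = 1.39, 164 per arm (328 total). Tests are two-sided (Significance levels section). From Background: "303 patients were randomised to surgery at one of 17 surgical centres". The number never operated on is not given, so it is an assumption below.

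**Step 1: what the 10% refers to.** Per arm before loss:

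n = 2 × [27 × (1.960 + 1.282) / 12]² = 106.4.

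Allowing for 10% loss, 106.4 / 0.9 = 118.2, the stated 118. (Rounding up to 107 first gives 119; the alternative 107 × 1.1 = 117.7 also rounds to 118.) Clustering: f = 1 + 13 × 0.03 = 1.39 and 118 × 1.39 = 164.0, the stated 164. On either way of applying the loss, the 10% inflates the number to be recruited. It is not a rate among operated patients, although the trigger presents it as the same quantity.

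**Step 2: what the written trigger can miss.** Let u be the number of the 303 who are never operated on and have no 52-week score. The trigger is unmet while the number of operated patients without a score is at most floor(0.10 × (303 − u)). The largest total without a score that leaves it unmet is

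T(u) = u + floor(0.10 × (303 − u)).

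| Assumed u | Operated | Most operated patients missing, trigger unmet | T(u) | Share of 303 |
|---|---|---|---|---|
| 0 | 303 | 30 | 30 | 9.9% |
| 5 | 298 | 29 | 34 | 11.2% |
| 10 | 293 | 29 | 39 | 12.9% |
| 20 | 283 | 28 | 48 | 15.8% |
| 30 | 273 | 27 | 57 | 18.8% |

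A threshold on all randomised patients would be crossed at 31 without a score (10% of 303 is 30.3). With u = 20 that means 11 operated patients missing (20 + 11 = 31); the written rule waits for 29.

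**Step 3: which part of the mismatch matters.** The change of denominator alone is small: 10% of 303 is 30.3 and 10% of 283 is 28.3, and the smaller base makes the trigger slightly easier to meet. The effect in the table comes from leaving the u patients out of the numerator.

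**Step 4: pooling of arms.** With 1:1 allocation, 15% missing in one arm and 4% in the other give (15 + 4) / 2 = 9.5% overall. The trigger is unmet. This holds even if every patient is operated on.

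**Step 5: time origin.** Set side by side, the 48 to 56 week window runs from surgery, while the ITT rule uses observed data from patients who had none. If such patients can contribute a score, the plan does not say when it counts as the 52-week score. If they cannot, they are missing, and the trigger does not count them. On either reading the sections need to be reconciled.

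**The case against.** A reader might infer more: that randomised patients who never have surgery drop out of both the ITT analysis and its safeguard. The text does not support that. No section excludes them from ITT. The two statements that address them, in the analysis-population section and under Abbreviations, include their observed data, and exclusion would have to be inferred from a window evidently written for operated patients. Visit timing for patients without surgery may also be set out in the protocol, which is not at hand. Nor are they outside the whole safeguard. The logistic regression is unconditional and not limited to operated patients, the imputation carries no such limit once triggered, and missing data, withdrawals and patients without surgery are all to be reported. Only the trigger leaves them out.

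It is also tempting to attach a bias in MOXFQ points. With 16% missing per arm, 10-point departures in opposite directions would shift the estimate by 0.16 × 10 + 0.16 × 10 = 3.2 points. A departure in one arm only gives 1.6, and equal departures in the same direction give zero. The documents support neither the departures nor the count behind the 16%, so no bias figure is claimed here.

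Finally, a pre-specified missingness threshold is a legitimate device, and the one-arm shifts partly answer the imbalance point once the analysis runs. Both are fair. Neither answers the objection to this threshold: its base differs from the population and the 10% that it invokes, and the one-arm shifts are not reached if the pooled rate stays at or below 10%. The descriptive regression gives context and is no substitute for an MNAR analysis.

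**Conclusion.** The point holds for the trigger. Its base (operated patients) conflicts with the ITT population and with the attrition allowance that it cites, and its pooled form can miss a one-sided loss. For an assumed 10, 20 or 30 unoperated patients, between 12.9% and 18.8% of those randomised could lack a 52-week score with no MNAR analysis. These are upper limits. They assume that none of the unoperated patients has a usable score and that missingness among operated patients lies just under the threshold. With no unoperated patients this gap is nil, and only the imbalance between arms remains.

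The missing time origin is a separate, smaller inconsistency; it is an undefined rule and not a stated exclusion.

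Severity is should-fix. The trigger governs a supportive analysis, and the primary model and estimate do not depend on it.

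**What to change.** 1. Run the tipping-point analysis already specified under Sensitivity analyses on all randomised patients, whatever the missing rate. At minimum, replace operated patients by randomised patients in the threshold and apply it in each arm separately.
2. State how any scores observed from patients without surgery are assigned to the 26- and 52-week visits, and count those without a score as missing, so that the outcome window, the ITT rule and the trigger agree. Timing from randomisation is one option, but it presumes that such scores were collected; the choice should follow what the protocol scheduled and what data exist.

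The first change costs a phrase in the SAP and a short extra analysis by a method already described. The second costs a sentence, provided that no new data are needed. Both should be settled before data lock, since deciding after the missing-data pattern by arm is known would be open to the charge of being data-driven.

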### Randomisation and blinding

The randomisation process was based on a minimisation algorithm. The algorithm gave an overall 85% chance of allocating the patient to the treatment arm which was under-represented with respect to three stratifying variables: surgeon, presence of OA in subtalar joint, and presence of OA in talonavicular joint (as determined by pre-operative MRI scan [7]). The research nurse or delegated individual logged on to the sealed envelope randomisation service and provided patient information (including on stratifying variables) and the surgical treatment to be received was supplied immediately.

Patients were allocated in a 1:1 ratio to the TAR and arthrodesis arms. It was not possible to blind patients, surgeons, radiologists, and clinical assessors for the following reasons: surgeons know what procedure they are performing, radiologists and patients will be able to identify from radiographs which procedure has taken place, and patients who receive ankle arthrodesis and their assessors will invariably know their ankle is stiff (a known consequence of arthrodesis surgery) whereas those undergoing TAR will retain motion in the ankle. To protect against allocation bias, the person recruiting the patient to the study was not aware of the allocation to be assigned prior to contacting the randomisation service.

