## Sample size

The sample size calculation for the primary outcome (change in MOXFQ walking/standing domain by 52 weeks post-op) was performed using Stata/IC version 12.1 [15]. It was based on achieving 90% power to detect the minimal clinically important difference (MCID) in the primary outcome at the 5% level of significance, accounting for expected loss to follow-up. The trial is multi-centre and the outcome plausibly varies by surgeon, so the sample size was adjusted to account for clustering; the intraclass correlation coefficient (ICC) was estimated based on previous studies, and the initially computed sample size was inflated by a factor f = 1 + (m − 1) ∗ ICC [16].

The sample size calculation was partly based on the study by Dawson et al. [9] which defined the MCID in the MOXFQ when evaluating outcomes following surgery for hallux valgus. They defined it as the mean change in MOXFQ of those patients who reported feeling at least “slightly better”, and found it to be 16, 12, and 24, respectively, for the standing/walking, pain, and social interaction domains of the MOXFQ. For this trial we determined it was important to detect a difference of 12 in the change from baseline in MOXFQ standing/walking domain between the two treatment arms; a conservative choice given the threshold for a MCID in the standing/walking domain found in the Dawson et al. study was 16. The standard deviation of the walking/standing domain of the MOXFQ was estimated as 27 [11], and loss to follow-up was estimated as 10% (attrition in similar RCTs has been 5–7% [17]).

Based on these quantities, the required sample size was estimated as 118 patients per arm. Assuming an average cluster size (m) of 14 (patients per surgeon) and an ICC of 0.03 (estimated from the median of ten previous surgical studies reporting patient-reported disease-specific measures 12 months post-surgery [18]), an inflation factor of f = 1.39 was estimated, leading to a final required sample size of 164 per arm or 328 patients total.

The assumptions of ICC = 0.03 and equal numbers of patients per surgeon in the sample size calculation [19] were reviewed by the trial statistician prior to the end of recruitment using the available data. The review indicated lower ICC and also some variability in numbers of patients per surgeon compared to the original assumptions (ICC < 0.01; average cluster size = 15, standard deviation = 9.6), resulting in increased power.

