### Significance levels of tests and confidence intervals

All statistical tests will use a two-sided *p* value of 0.05, unless otherwise specified. There will be no formal adjustment of *p* values for any interim analyses performed. Two-sided 95% confidence intervals will be presented for all estimates.

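### The number of imputations for the tipping-point analysis is set by loss of power, although the analysis reports Ø; the smallest numbers the rule allows leave Ø uncertain by several MOXFQ points

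*SAP article*

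**What the plan says.** The SAP article, under Sensitivity analyses, plans a pattern-mixture analysis if more than 10% of operated patients have no 52-week MOXFQ score. Missing scores are first imputed under missing at random. On how many imputations to use it gives one criterion: "The number of imputation datasets created, n, will be chosen to give a power reduction of" less than 1% relative to 100 imputations, with a citation. A number Ø is then added to the imputed scores and the results are combined by Rubin's rules. The shift Ø causing the p value "for the 52-week treatment effect estimate to cross the 0.05 boundary will be identified and reported". The search is repeated with the shift in the TAR arm only and in the arthrodesis arm only.

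The section does not say whether the 1% is absolute or relative, at what reference power it is judged, or what Monte Carlo error in Ø is acceptable.

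**The concern.** The criterion controls one quantity and the analysis reports another. Power depends on the average width of the pooled interval, which a handful of imputations already brings close to its limit when little information is missing. Ø is found by asking how far a small group of imputed patients must move to carry the overall estimate across a boundary. Any random error in the overall estimate is divided by the size of that group when it is turned into Ø. A number of imputations that is ample for power can therefore be too small for Ø.

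Ø is the number from this analysis that the SAP will use, together with the characteristics of patients without 52-week scores, to judge whether missing data could compromise the primary conclusion. If it carries several points of seed error and nothing in the report shows this, readers will take it as more exact than it is.

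**Working it through.** M is the number of imputations (the SAP's n). FMI is the fraction of missing information.

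**Inputs from the SAP.**
- Test level: "All statistical tests will use a two-sided" p value of 0.05.
- Design power 90%, where it was "important to detect a difference of 12 in the change from baseline".
- SD: "walking/standing domain of the MOXFQ was estimated as 27".
- Allocation: "Patients were allocated in a 1:1 ratio". Randomised: 303.
- Attrition: "loss to follow-up was estimated as 10"%. The analysis is triggered above 10%.

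**Assumptions not in the SAP.** Missing share 0.11 or 0.15. Baseline to 52-week correlation 0.3, and 26- to 52-week correlation 0.5 to 0.7. Half of those missing week 52 also miss week 26. These give an FMI of about 0.09 to 0.14; the power rule is examined for 0.10 to 0.20.

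**Step 1. The plan's own figure.** The SAP states no number of imputations, so the check on inputs is its sample size: 2 × (27 × (1.960 + 1.282)/12)² = 106.4 per arm; 106.4/0.9 = 118.2; f = 1 + 13 × 0.03 = 1.39; 118 × 1.39 = 164 per arm, 328 in total. This agrees with the SAP.

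**Step 2. What the power rule requires.** Rubin's total variance is W + (1 + 1/M)B. With B/(W + B) = 0.10 and W + B = 1, it is 0.9 + 1.2 × 0.1 = 1.020 at M = 5 and 0.9 + 1.01 × 0.1 = 1.001 at M = 100. The standard error rises by about 0.9% (√(1.020/1.001)). At 90% power this alone gives Φ(3.242/1.0095 − 1.960) = Φ(1.25), about 0.895, a loss of about 0.5 points. Allowing also for the randomness of B and for the degrees of freedom (Barnard-Rubin), the loss is 0.8 points at M = 5 and 0.3 at M = 10. The smallest M that meets the rule (absolute / relative 1%) is:

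| Reference power | FMI 0.10 | FMI 0.15 | FMI 0.20 |
|---|---|---|---|
| 90% | 5 / 5 | 7 / 8 | 9 / 10 |
| 78% | 6 / 7 | 9 / 11 | 12 / 14 |
| 50% | 6 / 10 | 8 / 15 | 11 / 20 |

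**Step 3. What those numbers do to Ø, one arm shifted.** Adding Ø in one arm moves the estimate by Ø × (missing share), so error in the estimate is multiplied by 1/0.15 = 6.7 to 1/0.11 = 9.1. The Monte Carlo variance of the pooled estimate is about FMI × SE²/M, hence

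SD(Ø) ≈ √(FMI × SE²/M) / share.

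Example: √(0.10 × 2.9²/5)/0.11 = 0.410/0.11 = 3.7.

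A simulation of the search on one fixed data set (303 patients, SD 27, ANCOVA at 52 weeks, estimate −8), changing only the seed, gives the right-hand columns. Its SDs are somewhat above the formula, which ignores variation in the pooled standard error.

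| M | Formula: share 0.11, FMI 0.10, SE 2.9 | Formula: share 0.15, FMI 0.14, SE 2.96 | Simulated SD | 95% seed range of Ø, 11% missing | 95% seed range of Ø, 15% missing, r = 0.5 |
|---|---|---|---|---|---|
| 5 | 3.7 | 3.3 | 4 to 5 | 8.7 to 24.2 | −0.2 to 20.2 |
| 10 | 2.6 | 2.3 | 2.5 to 3.2 | 11.6 to 21.6 | 4.8 to 16.6 |
| 20 | 1.9 | 1.7 | about 2 | not reported | 7.5 to 15.1 |
| 100 | 0.8 | 0.7 | 0.7 to 0.9 | 15.9 to 18.6 | 10.0 to 13.2 |

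**Step 4. Both arms shifted.** The estimate now moves only by Ø times the difference in missing shares. With 8% and 14% missing and an estimate of −8, the simulated SD is 5.6 at M = 5, 4.2 at 10 and 1.3 at 100 (95% ranges 18.8 to 38.8, 21.5 to 37.2 and 28.5 to 33.2). With 10% and 12% missing it is 8.7, 6.0 and 1.7. The simple multiplier 1/0.02 = 50 would overstate this last case (0.42 × 50 = 21 at M = 5), because a large Ø also widens the standard error and helps p across the boundary.

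**The case against.** **The minimum is not known.** The rule refers to a cited source that is not at hand, and 1% is undefined. A reader might infer that the rule means 5 to 10 imputations. That is only the lower part of the range: the table in Step 2 runs to 20, and the source may lead higher. This stands, and the point is stated for 5 to 20. Even 20 leaves an SD of about 2 points, or roughly ±4.

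**The rule is a floor.** Fifty or 100 imputations also satisfy it, and an article that condenses a fuller plan may leave out the final number and the seed. This stands too. A reader might infer that the reported Ø will be unstable; the SAP supports only that it could be, if the analysts stop near the minimum. The objection does not rescue the criterion, because a floor tied to power gives no protection to Ø.

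**There is no threshold for Ø.** A reader might infer that two seeds could put Ø on opposite sides of 12 and so reverse the verdict on robustness. The SAP does not support this. The 12 points are a between-arm target difference, Ø is a shift in the missing patients' scores, and the SAP neither compares them nor sets any cut-off. Ø is to be read with the missing-data logistic regression and information from sites.

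**Reach and assumptions.** The SAP expects up to 10% missing and cites 5 to 7% in similar trials, so the analysis may never run. The primary model is fitted by REML to observed data and uses no imputation. The correlations and missing shares are assumed, and the simulation leaves out the surgeon effects and the repeated-measures structure. All of this limits the weight of the point but does not remove the mismatch, since the multiplication by 1/share does not depend on the model details.

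**Conclusion.** The point holds in a limited form. The SAP ties the number of imputations to power, the wrong quantity for an analysis whose result is Ø. Near the minimum the rule allows, equally valid runs could report values of Ø several MOXFQ points apart on a 0 to 100 scale, and further apart when both arms are shifted with similar missing shares. At 100 imputations the one-arm SD falls below 1 point. These sizes rest on an assumed FMI, missing shares and between-visit correlations.

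The consequence is confined to a conditional sensitivity analysis. The primary estimate, its confidence interval and its p value are untouched. It deserves correction because the change is small and the affected number is meant to inform how far the primary conclusion can be trusted.

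**What to change.** Replace the power criterion with a precision criterion for Ø:

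- Use at least 100 imputations with a pre-set seed.
- Increase the number until the Monte Carlo standard error of each reported Ø (both arms, TAR only, arthrodesis only) is below a pre-stated size, for example 1 MOXFQ point.
- Report that error beside each Ø.

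Under the assumptions above, 100 imputations would meet a 1-point limit for the one-arm searches. The SD falls as 1/√M, so the two-arm examples would need about 100 × 1.3² = 169 and 100 × 1.66² = 276. Nothing need be added about reusing one set of imputations for every Ø; the SAP's description of imputing first and then editing the imputed scores already reads that way.

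The cost is one sentence in the SAP and computing time. No data, staffing or design change is needed.
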